## Abstract

**Background:**

The global aging population is expanding rapidly and many individuals have a particularly higher risk of malnutrition. Malnutrition can lead to impaired body function, morbidity, and mortality. Meeting nutritional requirements is a key strategy to minimize multiple debilitating adverse outcomes associated with malnutrition in the elderly.

Oral nutritional supplements (ONS) have been widely used as a dietary intervention for malnutrition in older adults. These supplements provide additional nutrients and calories to support nutritional requirements and have been shown to improve nutritional status, physical function, and quality of life in malnourished older adults.

**Methods:**

This is an open-label, randomized controlled, parallel-group study including 50 institutionalized older adults (aged > 60 years) with malnutrition or at risk of malnutrition, living in a selected elderly care institution in Colombo, Sri Lanka. The aim is to assess improvement in healthy body weight gain and body composition in older adults with malnutrition at risk of malnutrition by using an ONS. Older adults will be screened for malnutrition using the Mini Nutrition Assessment (MNA) tool and eligible participants randomized using the simple random sampling technique to intervention and control groups (1:1 allocation ratio). The intervention group will consume 200 mL of ONS before bed continuously for 12 weeks. The primary outcome is the percentage who achieved at least 5% weight gain in the intervention group compared to the control group. Nutritional status (anthropometric, biochemical, clinical, and dietary), body composition (dual-energy X-ray absorptiometry), frailty, functional capacity (hand grip strength, knee extension, and Barthel index) cognitive status (Montreal Cognitive Assessment), and physical activity will be assessed as secondary outcomes at baseline and at the end of the 12-week intervention. Some measurements (anthropometry, dietary, and functional assessments) will also be performed at the end of the 4th week. Data will be analyzed using SPSS V-23.

**Discussion:**

This study will determine whether the use of an ONS is effective in promoting healthy weight gain in older adults with malnutrition or at risk of malnutrition. In addition, investigating the impact of an ONS on multiple outcomes via clinical, nutritional, functional, and cognitive function will provide a more comprehensive understanding of the potential benefits of these supplements.

**Trial registration:**

Sri Lanka Clinical Trail Registry SLCTR/2022/021. Oct. 6, 2022.

**Supplementary Information:**

The online version contains supplementary material available at 10.1186/s13063-023-07622-4.

## Administrative information

Note: the numbers in curly brackets in this protocol refer to SPIRIT checklist item numbers. The order of the items has been modified to group similar items (see http://www.equator-network.org/reporting-guidelines/spirit-2013-statement-defining-standard-protocol-items-for-clinical-trials/).

## Introduction

### Background and rationale

Over the last three decades, the proportion of older adults aged 65 years and above globally increased by nearly 3% [1]. This proportion is projected to rise further from 9.1% in 2019 to 16.7% in 2050, reaching an estimated 1.5 billion older adults [1]. This aging trend will affect Asia the most, with nearly 1.0 billion older adults estimated to be living in Asia by 2050. According to a recent meta-analysis of 240 studies, the pooled prevalence of older adults at risk of malnutrition was 26.5% in the community and 45.6% in healthcare settings globally. The numbers are even higher in Asia, where the prevalence of malnutrition among elders has reached 29.8% in the community, and 48.0% in healthcare settings, respectively [2]. Social isolation, depression, staff control over feeding, use of anorexigenic drugs, and depression cause weight loss in institutionalized older adults [3]. Malnutrition in the elderly is commonly due to one or more of the following factors: inadequate food intake; food choices that lead to dietary inadequacies; illnesses that cause raised nutrient demand, increased nutrient loss, poor nutrient absorption, or a combination of these factors [3]. Nutritional inadequacy in older adults can be caused by a variety of physiological, pathological, sociological, and psychological causes [4].

Physiological changes in the digestive system, oral cavity, lean mass, and basal metabolic rate occur in people as they age [5, 6]. Disorders of the gastrointestinal system ranging from problems with dentition and swallowing to dyspepsia, esophageal reflux, delayed gastric emptying, atrophic gastritis, declined gastric acid secretion, constipation, and diarrhea are associated with poor dietary intake and nutrition malabsorption in the elderly [3, 7]. Loss of lean mass and a decline in basal metabolic rate (BMR) cause poor nutrient utilization and may influence appetite and food intake [3, 8]. Many diseases (e.g., thyroid, cardiovascular, and pulmonary disease) lead to unintentional weight loss by increasing the metabolic demand and reducing appetite and caloric intake [9]. Chronic diseases such as hypertension, diabetes mellitus, and cardiovascular diseases are managed with dietary restrictions and treated with medication that influences food intake [3]. Reduced functional status, both physical and cognitive, affects older adults' ability to shop for food and meal preparation [3], and inadequate social support and social isolation lead to apathy about food. Psychological disorders like depression are well-known causes of anorexia and weight loss [3, 10], and malnutrition resulting from these causes can have severe consequences on the overall health and well-being of the elderly.

Protein-energy malnutrition (PEM) is the most common form of malnutrition in older adults followed by micronutrient deficiencies [11]. PEM-related consequences increase the risk for loss of muscle and bone mass, in turn increasing the possibility of fractures, limitations in mobility, disabilities that ultimately lower capacity for independent living, and increased mortality [12]. Moreover, malnourished older adults are prone to infectious diseases, impaired wound healing, and slowed post-surgical recovery [13]. Hence, early detection of malnutrition and implementation of appropriate interventions are key strategies to reduce morbidity and mortality while improving overall health and quality of life.

Nutritional intervention for the elderly includes dietary counseling, technical or human assistance at mealtime, food fortification, texture adaptation, and prescriptions of energy- and protein-dense oral nutritional supplements (ONS) [14]. According to the guidelines by the European Society for Parenteral and Enteral Nutrition (ESPEN), enteral nutrition (EN) should be the first choice for older adults with normal gastrointestinal function who are malnourished or at risk of malnutrition [15]. As the first choice for EN, a specialized ONS can conveniently enhance the macro- and micro-nutrient intake [16]. A recent meta-analysis by Mengqi Li et al. found that ONS has beneficial effects on the overall appetite, energy intake, and body weight of malnourished older adults [17]. In addition, in a randomized, placebo-controlled trial of older adults in Singapore, a significant improvement in mid-upper arm circumference (MUAC) was observed in the intervention group who received a specialized ONS in comparison to the placebo group [18]. Another study among malnourished older adults with cardiovascular and pulmonary events found that ONS improved hand grip strength and contributed to overall recovery [19]. Most importantly, a study by Yue Zhong et al. showed that ONS cost-effectively extended the lives of malnourished hospitalized patients [20].

In this context, we designed an intervention study to evaluate the impact of ONS on healthy body weight gain (increase in muscle mass and fat mass), along with secondary outcomes in institutionalized older adults in Sri Lanka. In addition to weight gain, this study will assess the impact of an ONS on nutritional, functional, clinical, and cognitive outcomes and provide a comprehensive understanding of the potential benefits of using ONS as a nutrition intervention for malnourished older adults.

## Objectives

### Hypothesis

Providing an ONS for 12 weeks will increase the body weight of institutionalized older adults with malnutrition or at risk of malnutrition at least by 5%.

### General objective

To evaluate the impact of an ONS on the nutritional, clinical, cognitive, and functional status of institutionalized older adults during a 12-week intervention.

### Specific objectives

To investigate the impact of ONS on the following parameters among institutionalized older adults:

i.Anthropometric measurements — height, weight, mid-upper arm circumference (MUAC), calf circumference (CC), waist circumference (WC), and skin fold thicknessii.Body composition parameters — whole body dual-energy X-ray absorptiometry (DXA) scanningiii.Biochemical parameters — full blood count (FBC), Hs-CRP (C-reactive protein), total 25 hydroxy vitamin D, serum albumin, and total cholesteroliv.Functional capacity — hand grip strength, knee extension, and Barthel index scorev.Frailty five-fried model indicator scorevi.Peak expiratory flow ratevii.Systolic and diastolic blood pressureviii.Dietary intake — 24-hour dietary recallix.Physical activity level — Physical Activity Scale for the Elderly (PASE) and International Physical Activity Questionnaire (IPAQ)x.Cognitive status — Montreal Cognitive Assessment score (MoCA)

## Trial design

This study is a randomized-controlled, parallel-group, clinical trial that will include an intervention group (200 mL of high-energy and protein oral nutrition supplement daily before bed for 12 weeks) and a control group of older adults aged above 60 years who are malnourished or at risk of malnutrition. Participants satisfying the eligibility criteria will be allocated to control and intervention groups equally (1:1). The intervention length is 12 weeks. The CONSORT flow diagram of the trial is provided in Fig. 1. Items included in this protocol conforms to standards described in the SPIRIT (Standard Protocol Items: Recommendations for Interventional Trials) Checklist (Additional File 1).

**Fig. 1 Fig1:**
[figure not shown]
CONSORT flow diagram

## Methods: participants, intervention and outcomes

### Study setting

The proposed study will be conducted as an open-label, randomized controlled clinical trial, at a selected residential care facility registered in the National Secretariat for Elders in Colombo, Sri Lanka. Two parallel study groups will include a treatment group and a control group in the same study setting. The study will start with a screening visit to check eligibility.

### Eligibility criteria

Inclusion criteria:

Aged above 60 yearsResiding in the selected elder’s homes for more than one yearMalnourished or at risk of malnutrition (MNA score ≤ 11)

Exclusion criteria:

Presence of chronic illnesses — cardiac failure, stroke, chronic liver disease, and end-stage renal failure or undergoing dialysisThose who are unable to respond to the questionnaire due to communication difficulties (elders with speech, hearing, and visual impairment)BedriddenWho are on a special diet (supplements/tube feed)On an end-of-life care pathwayWithout the capacity to consent

### Who will take informed consent?

The investigators (PW, RJ) will obtain informed written consent from participants after explaining the potential benefits and risks of participation and the right to withdraw from the study.

### Additional consent provisions for collection and use of participant data and biological specimens

The information leaflet and consent form include details of the blood samples taken and the tests carried out. No additional consent will be obtained from the participants since biological specimens are not going to be stored for use in future studies.

## Intervention

### Explanation for the choices of comparators

Oral nutritional supplements have been shown to be well tolerated and have a high compliance rate in older adults [21, 22]. Therefore, choosing a specialized ONS can be a convenient and effective way to enhance nutrient intake in this population.

Eligible participants are randomized either into intervention or control group. Participants in the intervention group will consume the ONS before bed daily for 12 weeks in addition to their normal diet. Participants in the control group will be waitlisted and a glass of water will be received before bedtime.

### Intervention description

Before the baseline data collection, both the treatment and control groups will be given dietary advice, during which they will be educated on the importance of including each food group, developing healthy habits, avoiding alcohol and smoking, and maintaining a healthy level of physical activity. Subsequently, they will be randomized to treatment and control groups. During the 12-week study period, participants randomized to the ONS treatment group will receive a 200mL serving of an oral nutrition supplement (prepared by adding 4 level scoops of Entrasol Platinum, Kalbe (Pvt). Ltd (57g) into 200 mL of lukewarm water) daily before bed which contains 12 g protein and 247 kcal per serving, in addition to their usual diet for 12 weeks. The nutritional composition of the ONS is summarized in Table 1.

**Table 1 Tab1:** Nutritional composition (serving size: 4 scoops [57 g] of ONS)

		**% DV**	**Per serving**	**Per 100 g**
**Total calories**	kcal		247	434
**Total fat**	g	12	8	14
*SFA*	g	23	4.5	8
*MUFA*	g		2	3
*PUFA*	g		1	2
*Trans fatty acids*	g		< 0.5	< 0.5
*Cholesterol*	mg		< 0.5	< 0.5
**Protein**	g	20	12	21
**Total carbohydrate**	g	10	32	55
*Dietary fiber*	g	17	5	9
*Sucrose*	g		7	12.5
*Sodium*	mg	10	153	268
*Potassium*	mg	2.5	126	221
*Vitamin A*	mcg	30	184	323
*Vitamin B*_*1*_	mg	25	0.3	0.55
*Vitamin B*_*2*_	mg	25	0.4	0.71
*Vitamin B*_*3*_	mg	30	4.7	8.2
*Vitamin B*_*5*_	mg	40	2.1	3.6
*Vitamin B*_*6*_	mg	35	0.4	0.75
*Vitamin B*_*7*_*/Biotin*	mg	60	17.6	30.7
*Folic acid*	mcg	30	125	220
*Vitamin B*_*12*_	mcg	30	0.7	1.3
*Vitamin C*	mg	40	26.8	64.5
*Vitamin D*_*3*_	mcg	20	2.8	4.9
*Vitamin E*	mg	30	4.6	8.1
*Calcium*	mg	20	219	384
*Magnesium*	mg	8	26.6	46.6
*Phosphorus*	mg	15	88.7	156
*Iron*	mg	9	2.1	2.7
*Iodine*	mcg	30	46.2	81
*Zinc*	mg	30	3.9	6.8
*Chromium*	mcg	15	3.3	5.8
*Selenium*	mcg	15	4.1	7.2

*SFA* Saturated fatty acids, *MUFA* Monounsaturated fatty acids, *PUFA* Polyunsaturated fatty acids

### Criteria for discontinuing or modifying allocated intervention

A mechanism will be in place to ensure direct reporting of adverse events to investigators through the management of the elder’s home. Participants will be instructed to seek attention immediately. If there is an adverse event related to the study such as nausea, vomiting, diarrhea, bloating, and feeling of fullness, it will be notified immediately to the safety monitoring team, and the patient will exit the study and receive appropriate medical attention. Participants are allowed to withdraw from the study for any reason at any time.

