### Strategies to improve adherence to intervention

After starting the intervention, online video calls (WhatsApp or Viber) will be made to caregivers of the selected elderly care institution on a daily basis. The first call will be made to remind participants to ingest either treatment (200 mL of Entrasol Platinum) or control (200 mL of water), after dinner. A second call will be made to make sure whether all participants in the intervention group have consumed the supplement and all the participants in the control group have consumed an equal quantity of water. There will be random visits from the data collection team during the administration of ONS.

Compliance with ONS intake will be calculated over 12 weeks (84 days) using the participant's intake record and return of balance product containers. The percentage of compliance will be calculated by the following formula:

The number of supplement containers consumed is divided by the number of supplement containers instructed to consume, multiplied by 100.

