### Adverse event reporting and harms

A mechanism will be in place to ensure direct reporting of probable adverse events to the investigator by participants. In case of any adverse events immediate actions, immediate actions will be sought through the administration of the elder’s home.

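### Adverse events rely on spontaneous report and are escalated on an undefined, unblinded relatedness judgement, so gastrointestinal events and linked exits are liable to differential ascertainment between arms

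*Protocol article*

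**What the plan says.** Two sections of the protocol article describe how adverse events come to light.

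- Criteria for discontinuing or modifying allocated intervention provides for "direct reporting of adverse events to investigators through the management of the elder’s home" and adds that "Participants will be instructed to seek attention immediately". It then sets a condition for escalation: "If there is an adverse event related to the study such as nausea, vomiting, diarrhea, bloating, and feeling of fullness, it will be notified immediately". The recipient is the safety monitoring team. For such an event, "the patient will exit the study and receive appropriate medical attention".
- Adverse event reporting and harms gives a different reporter and a different qualifier: "A mechanism will be in place to ensure direct reporting of probable adverse events to the investigator by participants".

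The article does not say who decides that an event is related, on what criteria, or what is meant by probable. Under Interim analysis, termination also turns on serious adverse events related to the intervention.

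The other contacts with participants are set out under Strategies to improve adherence to intervention. Two video calls a day go to the caregivers and cover both arms. The first is a reminder. The second is a check on intake: "A second call will be made to make sure whether all participants in the intervention group have consumed the supplement", and that controls have drunk their water. The same section places random visits by the data collection team at the time the supplement is given.

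Participants are not blinded, and the Discussion says that blinding participants or investigators is not possible. An independent committee reviews accumulated data monthly.

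**The concern.** Each step between a symptom and the safety team passes through someone who knows the arm: the participant, the caregiver, the home's management, the investigator. The blinding of outcome assessors and data analysts does not help, because they are not described as noticing or classifying these events. Bloating after a 247 kcal drink is easily put down to the drink; bloating after a glass of water is not.

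Two things are at stake. First, what is said about tolerability. An excess in the supplement arm could come from unequal reporting. Few reports could be taken to confirm the statement under Provisions for post-trial care that no adverse effects are expected, in a section that also foresees giving the supplement to controls afterwards. Second, retention. Because a related event is tied to leaving the study, unequal labelling can produce unequal exits, in arms of only 25.

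**Working it through.** The article states no adverse-event figure, so there is nothing to reproduce. The check sets the sections side by side and then uses assumed inputs to show how strongly the result depends on unknown rates.

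**1. Is reporting solicited?** Neither reporting section describes anyone asking about symptoms. The one daily contact that covers both arms is described as a check on consumption. As described, ascertainment is spontaneous.

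**2. Where does relatedness enter?** Not at the first step: the home's management reports adverse events in general, in either arm. It enters at notification of the safety team and at exit. The judgement is undefined and made without blinding.

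**3. Is contact equal between arms?** The calls are. The random visits are tied to giving the supplement, and no counterpart is stated for the water.

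**4. Do the two reporting sections agree?** One routes adverse events through the home's management, the other has participants report probable events directly to the investigator. Both routes may be intended, but the text does not say so.

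**5. Illustration of scale.** Expected recorded cases = n × r × c, with n = 25 per arm (Sample size), r the true rate (assumed equal in both arms) and c the proportion captured (assumed).

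- Supplement: 25 × 0.20 × 0.90 = 4.5 (18%).
- Control: 25 × 0.20 × 0.30 = 1.5 (6%).

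The threefold ratio is simply 0.90/0.30, the assumed capture ratio returned.

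To show the range, take full capture in the supplement arm and a fraction of it in controls. The table gives the probability that a two-sided Fisher test at 5% signals a difference when the true rates are equal (exact enumeration, 25 per arm). The article plans no such test; it serves only as a yardstick.

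| True rate, both arms | Control capture 100% | 50% | 25% | 10% | 0% |
|---|---|---|---|---|---|
| 10% | 0.9% | 1.3% | 2.1% | 2.8% | 3.3% |
| 20% | 2.2% | 8.6% | 19.8% | 30.3% | 38.3% |
| 30% | 2.3% | 15.0% | 41.7% | 66.1% | 80.7% |
| 40% | 3.0% | 23.1% | 59.1% | 86.3% | 97.1% |

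The direction is the same throughout. The size runs from negligible to near certainty, depending on inputs the article does not give.

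**6. What silence would show.** With 0 events in 25, the one-sided 95% upper limit is 1 − 0.05^(1/25) = 0.113, about 11%, and only if capture was complete.

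**7. Link to the primary outcome.** The article expects under 5% missing primary data and imputes above that. If an exit also means no week-12 weight (an assumption), three exits in 50 (6%) pass that mark.

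**The case against.** A reader might infer that events are recorded only if thought related, that they will be captured almost only in the supplement arm, and that the arms cannot be compared. The text does not support this. The opening sentence on reporting covers adverse events without a relatedness or arm limit; relatedness governs notification and exit. Probable may just mean suspected, and the next sentence of that section refers to any adverse events. The calls and the week 4 and week 12 assessments cover both arms. The committee reviews accumulated data, not only escalated events.

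Two further supports are also weak. The Background lists "dyspepsia, esophageal reflux, delayed gastric emptying, atrophic gastritis, declined gastric acid secretion, constipation, and diarrhea" among gastrointestinal disorders in the elderly, but gives no frequency, and of the five symptoms named for escalation only diarrhea appears there. Nor can it be argued that impaired cognition is expected to prevent reporting: the article does not say so, and people without capacity to consent or unable to respond to the questionnaire are excluded.

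This is also a condensed article. Adverse-event forms, definitions and call scripts may sit in the full protocol, so the lack of an adverse-event row in Table 2 is not a finding in itself.

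Finally, active questioning has a price: as the sentence stands, more events found could mean more exits, against a 20% drop-out allowance.

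These objections narrow the point. What remains is that the method the article does state is spontaneous, with an undefined and unblinded causal judgement at the escalation step, differing routes, and visits tied to one arm.

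**Conclusion.** The point holds as a liability to differential ascertainment. Gastrointestinal events, their notification to the safety team and the exits linked to them can differ between arms for reasons other than the supplement. This rests on the stated reporting routes, the undefined relatedness condition, the open-label water control and the visits tied to supplement administration.

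Its size cannot be derived from the documents. The 4.5 against 1.5 cases and the table are illustrations on assumed rates, not estimates. The change is worth making because it is cheap and the calls already exist. The clinical merit of the exit provision is not judged here.

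**What to change.** 1. Strategies to improve adherence to intervention: on the second daily call, ask the caregiver the same fixed question for every participant in both arms, covering the five symptoms already named, hospitalisation, and any other new complaint. Record pre-existing symptoms at baseline.
2. Record all events regardless of relatedness, assign relatedness afterwards, and tabulate events by arm for the monthly committee.
3. Reconcile the reporting routes and wording of Criteria for discontinuing or modifying allocated intervention with those of Adverse event reporting and harms.
4. Have the investigators state how recording an event relates to the exit provision, so that solicited recording does not by itself change exits. No clinical exit rule is proposed.

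Cost: protocol wording and a short log, with no new visit or staff. Calls become slightly longer and more minor events are recorded. Some bias remains, because the caregivers who answer know the arm.

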### Outcomes

The primary outcome measure is the percentage of intervention group participants who achieved at least 5% weight gain compared to the control group.

The secondary outcome measures include mean between-group differences of the following variables from baseline to the end of the 12th week:

I.Anthropometric measurementsBody weightHeightBody mass index (BMI)Mid-upper arm circumference (MUAC)Calf circumference (CC)Waist circumferenceTriceps skin fold thicknessII.Body compositionDXA lean body mass and fat massIII.Biochemical parametersFull Blood Count (FBC)Hs-CRP (C-reactive protein)Serum albuminTotal cholesterolSerum total 25-hydroxy vitamin DIV.Functional capacityHand grip strengthKnee extensionActivities of daily living — Barthel indexV.FrailtyFive fried model indicatorsVI.Respiratory muscle strength (peak expiratory flow rate)VII.Energy and macronutrient intake per dayVIII.Cognitive status (Montreal Cognitive Assessment)IX.Physical activity levelPhysical Activity Scale for the Elderly (PASE)International Physical Activity Questionnaire (IPAQ – short form)

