### Sample size

The sample size calculation was based on studies indicating that a weight gain of 5% can be expected with an ONS intervention, and is sufficient to achieve an overall improvement in nutritional status [23]. A clinically relevant difference was defined as an increase in this fraction to 75% or greater in the treatment arm. Hence, a total of 50 adults will be recruited for the study (alpha, 5%; beta, 10%; drop-out rate, 20%) after the screening for eligibility against inclusion/exclusion criteria. Then, participants will be randomly assigned into two groups (*n*=25 intervention and *n*=25 control). The formula used for sample size calculation was as follows:$${n}_{B} =\left( \frac{{p}_{A \left( 1- {p}_{A}\right)}}{k} \right)+{\left(\frac{z1- \frac{\propto }{2 } + z1- \beta }{{p}_{A-{P}_{B}}}\right)}^{2}$$$${n}_{B}$$ = Sample size in one arm

*P*_*A*_ = Proportion of participants expected to achieve 5% improvement in body weight in the control group (0.3) [23]

*P*_*B*_ = Proportion of participants expected to achieve 5% improvement in body weight in the intervention group (0.75) [23]

*Κ* = Sampling ratio (1:1)

*Z*_*α*_ = Critical value of the normal distribution at *α* (*α* is 0.05 and the critical value is 1.96)

*Z*_*β*_ =Critical value of the normal distribution at *β* (*β* is 0.1)

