### Procedure for unblinding if needed

Participants will not be blinded, given the nature of the study intervention. Single blinding of the outcome assessors and data analysts will be maintained throughout the study.

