### Methods in analysis to handle protocol non-adherence and any statistical methods to handle missing data

Each participant’s consumption of the ONS will be monitored on a weekly basis to assess adherence to the intervention. If a participant is unable to consume the supplement continuously for more than five days due to hospitalization or any other reason, they will be considered as “non-adherent” to the intervention. Using Multiple imputation methods accessible in SPSS, the primary outcome data of the participants will be randomized to the intervention but non-adherent participants will be imputed [29].

We expect the proportion of missing data to be below 5% for the primary outcome. We will not perform multiple imputations for the primary outcome unless more than 5% of the data are missing. The secondary outcomes will be assessed in a full analysis set.

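### Ending study participation after a study-related adverse event, with no provision for a later week-12 weight, tilts the primary comparison towards ONS

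*Protocol article*

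**What the plan says.** The rule stands in the protocol section on discontinuing or modifying the allocated intervention. Its trigger is: "If there is an adverse event related to the study such as nausea, vomiting, diarrhea, bloating, and feeling of fullness". Its consequence is: "it will be notified immediately to the safety monitoring team, and the patient will exit the study and receive appropriate medical attention". The section then adds a second route out, open to both arms: "Participants are allowed to withdraw from the study for any reason at any time".

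Other parts of the protocol bear on this:

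- **Comparator:** "Participants in the control group will be waitlisted and a glass of water will be received before bedtime".
- **Blinding:** "Participants will not be blinded, given the nature of the study intervention". Outcome assessors and analysts are to be blinded.
- **Primary outcome:** "The primary outcome measure is the percentage of intervention group participants who achieved at least 5% weight gain compared to the control group". Weight is scheduled at baseline, week 4 and week 12.
- **Missing data:** "We expect the proportion of missing data to be below 5% for the primary outcome". Multiple imputation of the primary outcome is reserved for the case where more than 5% is missing. The same section classes anyone off the supplement for over five days, whatever the reason, as non-adherent. In a garbled sentence it appears to say that their primary outcome will be imputed.
- **Sample size:** the calculation includes "drop-out rate, 20" per cent as an overall allowance.
- **Post-trial care:** no adverse effects are expected, and no event rate is given.

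**The concern.** The section deals with stopping the intervention, but its stated consequence is leaving the study. These are different events. A participant who can no longer take the supplement still lives in the home where weights are measured and can usually still be weighed.

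The named events are gastrointestinal reactions that a nutritional supplement can cause and a glass of water hardly can, and they must be related to the study to count. Losses caused by this rule will therefore fall mainly in the ONS arm. Those who leave have gastrointestinal symptoms and no longer take the supplement, so they are plausibly less likely to reach a 5% gain. Removing them raises the observed ONS rate without changing the control rate. A later analysis plan cannot restore weights that were never taken.

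**Working it through.** **1. Plan's own figure.** Inputs from the Sample size section are control rate 0.30, ONS rate 0.75, two-sided alpha 5% (z = 1.96), beta 10% (z = 1.2816) and 20% drop-out. The usual unpooled formula gives

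n = [0.30 × 0.70 + 0.75 × 0.25] × [(1.96 + 1.2816) / 0.45]² = 0.3975 × 51.89 = 20.63 per arm.

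Then 20.63 × 1.2 = 24.75, so 25 per arm and 50 in total. The planned number is reproduced, and about 20 to 21 evaluable participants per arm is what it assumes.

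**2. Imputation trigger.** I read the 5% as applying to both arms together: 0.05 × 50 = 2.5. Two missing weights (2/50 = 4%) lead to no imputation; three (3/50 = 6%) do. Two exits, if both are on ONS, are 2/25 = 8% of that arm.

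**3. Bias when nothing is imputed.** Assumptions: *e* of 25 ONS participants exit, no controls are lost, ONS completers gain at 75% (the planned rate), and a fraction *q* of exiters would have gained at least 5%. I take *q* from 0 to 0.30, the upper end being the planned control rate.

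True ONS rate = [(25 − e) × 0.75 + e × q] / 25, so overstatement = (e/25) × (0.75 − q).

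| ONS exits | True rate, q = 0.30 | True rate, q = 0 | Overstatement |
|---|---|---|---|
| 0 | 75% | 75% | 0 |
| 1 | 73.2% | 72.0% | 1.8 to 3 points |
| 2 | 71.4% | 69.0% | 3.6 to 6 points |

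**4. The same two exits when ONS has no effect.** Suppose the true rate is 30% in both arms and both exiters are non-gainers. The expected observed ONS rate is 25 × 0.30 / 23 = 32.6%, an overstatement of 2.6 points. By exact binomial enumeration with 25 per arm, the chance of a significant result favouring ONS (nominal 2.5%) rises from 2.7% to 4.6% with a chi-square test, and from 1.1% to 2.7% with Fisher's exact test. The choice of test is my assumption, and this is a worst case for two exits.

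**5. Three or more missing.** The plan would then impute. Standard multiple imputation assumes missing at random. Here the reason for loss is intolerance and the end of supplementation, and at most a week-4 weight informs the model; for those who leave before week 4 there is none. If imputation merely reproduced the completers' rate, three ONS exits would still leave (3/25) × (0.75 − q) = 5.4 to 9 points. An informative week-4 weight would reduce this, by an amount that the documents do not allow one to calculate.

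**The case against.** The strongest reply is that exit may be loose wording for stopping the product, given the heading it stands under. The section on the Mini Nutritional Assessment plans that measurement for all residents in both groups after 12 weeks, and the post-trial care section plans screening for malnutrition at the end. So a reader should not infer that the protocol forbids a week-12 weight; it does not say so. But neither section says that someone who has exited is weighed for the primary outcome, and the wording of the rule points the other way.

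Four stronger readings are tempting but not supported:

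- **A bias of 9 to 15 points.** This follows from five ONS exits, (5/25) × 0.45 and (5/25) × 0.75. The 20% behind it is an overall drop-out allowance, which the protocol's discussion links to the number of tests that both arms undergo. Five exits are also 10% of 50, so the plan would impute, and a completer analysis would not be its estimate.
- **Loss of power.** An ONS arm of 20 is about what the sample size formula requires (20.63). The harm is bias.
- **Missing weights almost only on ONS.** That describes losses caused by this rule. Unblinded, waitlisted controls can also withdraw.
- **Exiters are simply dropped.** The missing-data section may class them as non-adherent and impute their outcome. That keeps them in the analysis, but with a modelled value where an observed one could have been had.

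It is also fair that the protocol expects no adverse effects and describes ONS as well tolerated. This bears on the size of the bias but not on its direction.

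**Conclusion.** The point holds in a limited form. As written, the rule ends study participation for treatment-related reasons, and nothing in the protocol secures the primary outcome afterwards. When the rule operates, the resulting loss falls mainly on the ONS arm and plausibly favours it.

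The size cannot be fixed from the documents and may be zero. With two ONS exits and no imputation, the illustration gives 3.6 to 6 points on the ONS rate. It rests on completers at 75%, 0 to 30% of exiters gaining, and no control losses. Beyond that, the planned imputation does not reliably remove the bias, and what remains is unknown. That exiters are less likely to gain is a reasoned inference; the protocol gives no data on it.

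**What to change.** Amend the discontinuation section to separate stopping the supplement from withdrawing from the study. Participants who stop ONS remain in follow-up for the week-4 and week-12 weights, and for other assessments if willing, unless they withdraw consent or die. Analyse their observed weights in the allocated arm.

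Reconcile the missing-data section with this: where a non-adherent participant has an observed primary outcome, use it, and impute only what is truly missing. When the supplement is stopped remains for the investigators to decide; nothing here changes that.

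The cost is an amendment, which the protocol requires the ethics committee to approve before implementation, and a few extra weighings in a residential home. Recruitment began in February 2023, so weights already missed cannot be recovered.
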